## Abstract

**Aim:**

To evaluate the effects of internet‐based support program for primiparous women in terms of improving the levels of maternal self‐efficacy, social support, and satisfaction; and reducing their postpartum depression symptoms.

**Design:**

A single‐blinded, multicentre, randomized, controlled, parallel‐group pre‐test and repeated post‐test design.

**Methods:**

Based on the self‐efficacy theory and the social exchange theory, the internet‐based support program has five modules: (a) learning forum of parenting knowledge and skills; (b) communication forum; (c) ask‐the‐expert forum; (d) baby home forum; and (e) reminder forum. Primiparous women will be recruited in the obstetric wards of two university‐affiliated hospitals in China. The participants (*N* = 258) will be randomly allocated to the intervention group that receive routine care and access to the internet‐based support program and the control group that receive routine care during the 3 months postpartum. Maternal self‐efficacy, social support, and postpartum depression symptoms will be measured at baseline, immediately after the intervention (post‐test 1) and 3 months after the intervention (post‐test 2). The study was funded in January 2018 and was ethically approved in May 2020.

**Discussion:**

If the internet‐based support program has positive outcomes, it will contribute to the scientific and practical knowledge of nursing interventions to support primiparous women on parenting; and could become the routine health care for health professionals to enhance parenting ability and mental well‐being of new mothers.

**Impact:**

As the first RCT study on parenting outcomes using a rigorous research design and a theoretical framework in China, this research will contribute to evidence on the effectiveness of using internet platform to support women after childbirth. The results could help to advance research about the use of internet‐based intervention methods to improve women's maternal self‐efficacy, social support, satisfaction, and to alleviate depression symptoms.

Chinese Clinical Trial Registry: ChiCTR2000033154

## INTRODUCTION

1

Primiparous women usually confronted with many parenting problems in the early motherhood, which had a negative impact on the well‐being of mothers and infants (Zheng, Morrell, & Watts, 2015, 2018a). As an important predictor of parenting (Li & Liu, 2019), maternal self‐efficacy (*MSE*) is the belief of a mother holds of her capability about the organization and performance of parenting tasks (Montigny & Lacharite, 2005). Researchers found that the samples of women in the UK (Whittaker & Cowley, 2012), USA (Fulton, Mastergeorge, Steele, & Hansen, 2012), Finland (Salonen et al., 2009), and Canada (Pierce et al., 2010) had a high level of *MSE*; however, Chinese primiparous women had a moderate level of *MSE* and especially were less sure of their capability in recognition and management of some common diseases and emergency care for their infants (Zheng, Morrell, & Watts, 2018b).

Many factors are reported to affect *MSE* and the two main factors relating to *MSE* are postpartum depression (PPD) and social support (Zheng, Morrell, & Watts, 2018a). Evidences demonstrated that a greater proportion of Chinese primiparous women had PPD than women in Western countries, owing to the high expectations of being mothers and the sensitive and stressful relationship with their mother‐in‐law in Chinese culture (Gao, Chan, & Sun, 2012; Zheng et al., 2018b). The literature consistently showed that social support has a positive impact on *MSE* in various countries (Leahy‐Warren & McCarthy, 2011; Shorey, Chan, Chong, & He, 2015a). Studies, for example, by Zheng et al. (2018b) suggested that Chinese primiparous women receive inadequate support from health professionals, and they experienced a lack of informational and appraisal support on various newborn‐care tasks.

To enhance the parenting outcomes, some interventions were conducted for new mothers. For example, a randomized controlled trial (RCT) in Spain assessed the outcomes of a mindfulness‐based intervention on maternal psychological distress, well‐being, and *MSE* in breast‐feeding mothers (Perez‐Blasco, Viguer, & Rodrigo, 2013). The intervention was carried out over the meditation course of 8 weeks at a rate of one 2‐hr session per week. Compared with the control group, mothers in the treatment group had significantly higher *MSE* scores (*F* = 10.83, *p* = .004) from pre‐test of 78.85 (*SD* 9.00) to post‐test of 88.92 (*SD* 6.71). Moreover, mothers who received the treatment exhibited significantly less anxiety, stress, and psychological distress. In mainland of China (Gao et al., 2012; Gao, Sun, & Chan, 2014), a RCT was to examine the effects of interpersonal psychotherapy‐oriented childbirth education program consisted of two 90‐min group education sessions and one telephone follow up within 2 weeks after childbirth. The study group had a significantly higher level of social support (65.92 *SD* 8.10) (*t* = 2.33, *p* = .021), *MSE* (37.00 ± 5.13) (t = 2.43, *p* = .016), and less depressive symptoms (5.61 *SD* 3.33) (t = 2.39, *p* = .018) at 3 months postpartum when compared with the control group (their corresponding scores were 63.11 *SD* 8.67; 35.21 *SD* 5.14; 6.87 *SD* 3.97).

Evidence suggested that the traditional face‐to‐face interventions of parenting did have an effect; however, the feasibility and generalizability of traditional interventions were challenged by the huge number of primiparous women, the insufficient financial commitment to health care from the government (5.5% of the GDP), and the shortage of health professionals in China (Zhu, Ebert, Liu, & Chan, 2017). Fortunately, the development of E‐health and M‐health technologies provides alternatives to promote interaction between health professionals and patients outside the clinic (Mobasheri et al., 2014). Due to its convenience and increased accessibility, internet has potential to provide a promising platform for medical interventions (Zhu et al., 2017). In 2019, 61% of the Chinese population used the internet via mobile or computer devices (China News, 2020). The support program based on internet could provide an innovative and easily accessible intervention approach that can reach larger groups of women (Van den Berg, Gielissen, Ottevanger, & Prins, 2012). In Finland, a quasi‐experimental design was used to evaluate the effectiveness of an internet‐based intervention to support maternal satisfaction and *MSE* (Salonen et al., 2011). To the best of our knowledge, no RCTs by internet have been conducted in China on parenting outcomes for primiparous women.

## BACKGROUD

2

Transition to motherhood will bring various changes to the lives of women, who need to gain parenting knowledge and skills, adjust to the new household relationship, and fulfil self‐expectations as mothers (Salonen et al., 2011). Many women find it difficult to manage these physical, social, and psychological challenges in the early motherhood (Kunseler, Willemen, Oosterman, & Schuengel, 2014; Law et al., 2019); especially for the first‐time mothers owing to the lack of previous parenting experience (Leahy‐Warren & McCarthy, 2011).

The traditional face‐to‐face interventions, such as lecture and home visiting, were proved to be effective in the improvement of parenting outcomes; however, the feasibility and generalizability of these traditional interventions methods were challenged by the huge number of primiparous women and the shortage of health professionals in China. Thus, the alternative, innovative, and easily accessible intervention approach need to be designed. Evidence showed that internet interventions can contain more channels of media to tailor information, reach larger groups of women, and can provide more anonymity compared with face‐to‐face interventions (Van den Berg et al., 2012). Therefore, the internet‐based support program (ISP) for Chinese primiparous women will be conducted to improve their parenting ability, social support, and well‐being.

The theoretical framework of ISP was based on the Bandura's self‐efficacy theory (Bandura, 1997) and the social exchange theory (House, 1981). Bandura (1997, p.3) defined self‐efficacy as “a belief in one's abilities to organize and execute the course of action required to attain a goal or perform a certain task” and believed that self‐efficacy affected the regulation and maintenance of behaviour. Four major elements were identified that affected self‐efficacy: (a) previous experience; (b) vicarious experience; (c) verbal persuasion; and (d) physiological and emotional states (Bandura, 1997). Previous experiences involve previous personal accomplishments and successes. Vicarious experiences are gained by watching others achieve success in similar situations. Verbal persuasion comes from verbal cues and feedback from others. Physiological and emotional states are defined as a person's perception of his/her physical and mental state.

Social support involves both the perception of available assistance and satisfaction with received support (Tietjen & Bradley, 1985); and could be conceptualized by structural and functional components (House, 1981). The structural social support has been conceived as social network, which may be informal (family members, friends) or formal (health professionals), depending on the relationship with its recipient. The functional social support has been conceived as informational, instrumental, emotional, and appraisal support (House, 1981).

It is said that the appropriate levels of self‐efficacy and social support are essential components of interventions to improve maternal parenting outcomes (Shorey, Chan, Chong, & He, 2015b). The ISP aims to enhance *MSE* and social support to promote mothers’ ability to complete various parenting tasks, thus, improving their psychological well‐being. The multicomponent intervention of ISP program includes a learning forum, a communication forum, an ask‐the‐expert forum, a baby home forum, and a reminder forum that derived from the four factors of the self‐efficacy theory and the functional and structural social support concepts of the social exchange theory. For example, in terms of self‐efficacy theory, the previous experiences involve the provision of parenting knowledge and skills in the learning forum and reminder forum. Vicarious experiences include the parenting techniques taught through multimedia resources in the learning forum, and the sharing parenting experience and the feeling of motherhood transition in the communication forum and baby home forum. Verbal persuasion comes from feedback and suggestions from health professionals and other mothers in the ask‐the‐expert forum and communication forum. The above learning materials, the sharing of experiences, and the various supports from health professionals and other mothers may modify women's physiological and emotional states. According to the social exchange theory, the structural social networks of women are built and the various kinds of functional supports are provided from the health professionals and others through the designed communication forum, ask‐the‐expert forum, and baby home forum. The theoretical framework of the ISP is shown in Figure 1.

**Figure 1 jan14517-fig-0001:**
[figure not shown]
The theoretical framework of the ISP adapted from Shorey et al. (2015b). Note: *MSE*, Maternal self‐efficacy; PPD, Postpartum depression; ISP, Internet‐based support program [Colour figure can be viewed at wileyonlinelibrary.com]

## THE STUDY

3

### Aim

3.1

This study aims to evaluate the effects of ISP for Chinese primiparous women in terms of improving the levels of *MSE*, social support, and satisfaction; and reducing their postpartum depression symptoms.

The study hypothesizes that compared with the control group at baseline, post‐test 1, and post‐test 2, women in the intervention group will report statistically significant:
Improved *MSE* and social support;Reduced postpartum depression symptoms; and.Great satisfaction with healthcare received after childbirth.

### Design

3.2

#### Trial design

3.2.1

A single‐blinded, multicentre, randomized, controlled, parallel‐group pre‐test, and repeated post‐test design will be conducted to investigate the effect of the ISP for Chinese primiparous women in the initial postpartum period. The study follows the SPIRIT 2013 Statement and the guidelines for the Standard Protocol of Clinical Trials (Chan et al., 2013). The Consolidated Standards of Reporting Trials (CONSORT) (Schulz, 2011) flowchart is presented in Figure 2.

**Figure 2 jan14517-fig-0002:**
[figure not shown]
CONSORT flowchart of the study adapted from Schulz et al. (2011). Note: SICS: the Self‐efficacy in Infant Care Scale; EPDS: the Edinburgh Postnatal Depression Scale; PSSS: the Postpartum Social Support Scale

#### Study setting and participants

3.2.2

The research will be carried out in the two university‐affiliated tertiary public hospitals in China, where the live births in each study hospital are over 2,000 babies per year. The inclusion criteria will be: first‐time mothers with healthy babies; aged 18 years or above; married; and able to response the questionnaires. Exclusion criteria will be: women or their children have severe physical and mental diseases.

Sample size will be estimated based on previous research with a medium to small effect size (Cohen, 1992). With a power of 0.80, an alpha set at 0.05, and an effect size of 0.35 for the primary outcome of PPD (EPDS scores), each group will be 90 women (Gao et al., 2012). We estimate a 30% attrition rate based on an attrition rate of 9%–29% in previous research (Gao et al., 2012). A minimum of 258 women (129 in each group) are required.

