### Limitations

4.1

Some limitations need to be noted in the research. First, due to the nature of the research, blinding of researchers during all the research process is not possible and it may lead to the potential biases. Secondly, the participants are limited to those who are willing to participate in this study via internet. The results might not be generalized to those who refused to participate in the research or those who are not available to the internet. Thirdly, the longer‐term intervention will be conducted in this study and some participants may be loss during the follow‐up that can decrease the study power. To overcome the problems, a 30% attrition rate is considered in the sample size calculation and an ITT analysis will be performed in the research.

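### The stated 90 women per group gives about 65% power, not 80%, at an effect size of 0.35 (two-sided, unadjusted); 129 per group is what 80% power needs before any attrition

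*Protocol article*

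**What the plan says.** Section 3.2.2 (Study setting and participants) of the protocol article sets the design values: "With a power of 0.80, an alpha set at 0.05". It continues with "an effect size of 0.35 for the primary outcome of PPD (EPDS scores), each group will be 90 women", citing an earlier trial, and describes the basis as "previous research with a medium to small effect size". It then assumes 30% attrition, against 9% to 29% in earlier research, and concludes: "A minimum of 258 women (129 in each group) are required". Section 4.1 (Limitations) relies on the same allowance as the answer to lost power, saying that "a 30% attrition rate is considered in the sample size calculation".

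Allocation is 1:1 (section 3.2.4). The sample size paragraph gives no sidedness, no correlation between repeated measurements and no gain from covariates.

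**The concern.** The paragraph prints a complete set of inputs and a result, so the result can be checked. It looked too small: the usual two-group calculation for a standardised difference of 0.35 gives a number close to 129, which is the figure the article reaches only after adding its attrition allowance.

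At stake is the power claim for depression symptoms, the outcome on which the trial is sized. If 90 completers per group is too few, the 30% allowance does not protect 80% power as section 4.1 implies. The chance of missing the planned effect would be about 35% rather than 20%, and a null result could be taken as evidence against the program when the trial was not large enough to say so.

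**Working it through.** **Inputs.** From section 3.2.2: power 0.80, alpha 0.05, effect size 0.35, 90 per group, 30% attrition, 129 per group enrolled. From section 3.2.4: 1:1 allocation. Sidedness is not stated, so both were tried.

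**1. The plan's attrition step reproduces.** 90 / (1 − 0.30) = 128.6, so 129 per group and 258 in total.

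**2. What kind of effect size is 0.35?** The introduction gives 3-month depression scores from the earlier trial that the sample size paragraph cites: "less depressive symptoms (5.61", SD 3.33, in the intervention group and 6.87, SD 3.97, in the control group.

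- Pooled SD = √[(3.33² + 3.97²)/2] = 3.664
- d = (6.87 − 5.61)/3.664 = 1.26/3.664 = 0.344

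This agrees closely with 0.35 read as a standardised mean difference, and makes a misprint for 0.42 unlikely. Read instead as Cohen's f, 0.35 corresponds to d = 0.70 and needs about 34 per group, which is not 90 either.

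**3. Number needed per group.** n = 2(z₁₋α/₂ + z₀.₈₀)² / d²

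- Two-sided: 2(1.960 + 0.842)² / 0.35² gives 129 (normal approximation). The noncentral t gives 129.1, so 130.
- One-sided: 101 (normal approximation). The noncentral t gives 101.6, so 102.

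Neither is 90.

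**4. Power with 90 per group.** Power ≈ Φ(d√(n/2) − z₁₋α/₂)

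- Two-sided: Φ(0.35 × √45 − 1.960) = Φ(0.388) = 65.1%. Noncentral t: 64.6%.
- One-sided: Φ(2.348 − 1.645) = Φ(0.703) = 75.9%. Noncentral t: 75.6%.

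**5. Detectable difference with 90 per group at 80% power, two-sided.** (1.960 + 0.842) × √(2/90) = 0.418; noncentral t: 0.420. With the SD of 3.664, that is 0.42 × 3.664 = 1.5 points, against 0.35 × 3.664 = 1.3 points planned.

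**6. Two-sided power with 129 enrolled per group, by attrition (noncentral t).**

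| Attrition | Completers per group | Power at d = 0.35 |
|---|---|---|
| 0% | 129 | 80.0% |
| 9% | 117 | 76% |
| 29% | 92 | 65–66% |
| 30% | 90 | 65% |

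**7. Enrolment that would support the claim as stated.** 130 / 0.70 = 185.7, so 186 per group and 372 in total (two-sided, unadjusted).

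**8. Correlation that would rescue 90.** With baseline adjustment and one post-test, n is multiplied by (1 − ρ²). Setting 130(1 − ρ²) = 90 gives ρ = √(1 − 90/130) = 0.555. At ρ = 0.50 the need is 130 × 0.75 = 97.5 per group, still above 90.

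**The case against.** The strongest reply is that the planned analysis (section 3.2.8) is a covariate-adjusted repeated-measures MANCOVA over three time points, not a t test, and the sample size paragraph names no test. Repeated measurement can cut the number needed. If the mean of the two post-tests is adjusted for baseline, the factor is (1 + r_post)/2 − r_base², where r_post is the correlation between the post-tests and r_base the correlation of each with baseline. Taking 130 as the base and the same effect at both post-tests:

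- r_base 0.4, r_post 0.6: 130 × 0.64 = about 83 per group
- r_base 0.3, r_post 0.6: 130 × 0.71 = about 92
- r_base 0.2, r_post 0.7: 130 × 0.81 = about 105

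So 90 can be enough under some assumptions, and the 0.55 threshold applies to a single post-test only. This much stands: 65% is the power of an unadjusted comparison at one time point, not a certain value for the final model. It does not rescue the statement. None of these correlations is in the document, section 3.2.8 names only sociodemographic covariates, and section 3.2.3 groups post-test 1, not post-test 2, with the primary endpoints.

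A second reply is that sidedness is open and the hypotheses in section 3.1 are directional. One-sided, 102 completers suffice, so 129 enrolled would hold 80% up to 1 − 102/129 = 21% attrition. That limits the claim that 258 works only with no loss to two-sided testing. But 90 still falls short one-sided, and the F test of a MANCOVA is not directional.

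Third, 65% belongs to the planned 30% attrition; at 9% it would be 76%. Also, the introduction does not name the scale behind the depression scores, so the match with 0.35 is a close inference. Finally, an article may leave the test and correlation to a fuller document. The error here is not their absence, but a printed result that disagrees with the printed inputs.

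**Conclusion.** The sample size statement is wrong as written. At d = 0.35 and alpha 0.05, 90 completers per group gives 65% power two-sided or 76% one-sided, not 80%; 130 or 102 per group would be needed. Two-sided power is overstated by about 15 percentage points, and the 129 enrolled per group meets the requirement only with full retention.

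These figures rest on reading 0.35 as a standardised mean difference and on an unadjusted comparison at one time point. The failure of 90 to reproduce holds for either sidedness. The trial's power under its planned model could be higher, but nothing stated supports a figure.

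**What to change.** Keep 258 women, since recruitment began in May 2020, and correct the statement in section 3.2.2. For example:

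> With 129 women per group and 30% attrition (90 completers per group), the trial has 65% power for a standardised difference of 0.35 in EPDS score, or 80% power for 0.42 (two-sided alpha 0.05, unadjusted comparison).

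If an adjusted or repeated-measures calculation was intended, state instead the analysis, the time point and the assumed correlation (at least 0.55 for one baseline-adjusted post-test), with a source for it from earlier data rather than a value chosen to arrive at 90. Amend section 4.1 so that it no longer presents the 30% allowance as securing power.

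The cost is wording only, with a less favourable power figure. Keeping 80% power at 0.35 with 30% attrition and no adjustment would instead take 372 women, 372 − 258 = 114 more.

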#### Recruitment

3.2.3

Participants will be recruited when women are admitted in the obstetric wards of hospitals. The obstetric nurses will introduce the ISP to women who meet the inclusion criteria. Posters and leaflets about the program also will be strategically distributed in the obstetric wards to inform all women and their family members. Women who verbally agree to participants will be approached by the researchers to provide them with an information sheet and to answer their any questions about the research. In this approach, women were not asked to give consent as it was considered important to make sure that women had enough time (at least 1 day) to read the information sheet, think about participation, and discuss it with their family members. The researchers will acquire participants’ written informed consent on the next day.

The recruitment period is expected to extend over a 3‐month period. Data will be collected before randomization (baseline), immediately after the intervention (post‐test 1), and 3 months after the intervention (post‐test 2). Recruitment of participants began in May 2020. Primary endpoints (baseline and post‐test 1) and follow‐up measure (post‐test 2) will be expected to be completed in January 2021.

#### Randomization and blinding

3.2.4

The Research Randomizer will be used to randomly assign participants into the experimental group and the control group with a distribution ratio of 1:1. The allocation sequence will be put into the opaque and sealed envelopes. Blinding will not be possible for the researchers during all the research process; however, the group allocation will be masked during the recruitment until the baseline measures are completed. In terms of trial participants, outcome assessors, and data analysts, they will be blinded to the participants’ group allocation.

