#### Intervention

3.2.5

The women in the control group will receive routine care. Routine care consists of supports from the obstetricians and obstetric nurses during the 3–5 days hospitalization; and home visits from the community doctors on the 3rd, 7th, 14th, and 28th days postpartum (Zheng, Morrell, & Watts, 2015). The women in the study group will have access to the ISP and receive routine care in the postpartum period. The details of intervention are described in Table 1.

**Table 1 jan14517-tbl-0001:** The details of intervention

	Intervention Group	Control Group
Service	ISP + routine care	Routine care
Provider	Researchers	Obstetricians, obstetric nurses, community doctors
Place	Web environment	Hospital, home
Form	Internet	Face‐to‐face
Contents	Learning forum Communication forum Ask‐the‐expert forum Baby home forum Reminder forum	Routine postpartum home visiting
Duration and frequency	From childbirth to 3‐month postpartum The total intervention time not less than 12 weeks Reminder telephones every week, reminding them to log in the ISP at least twice a week, and no less than total 1 hr per week	From childbirth to 1 month postpartum At least two home visits
Assessment	Baseline (pre‐intervention) Post‐test 1 (immediately after intervention) Post‐test 2 (3 months after intervention)	Baseline (pre‐intervention) Post‐test 1 (immediately after intervention) Post‐test 2 (3 months after intervention)

Abbreviations: ISP, Internet‐based Support Program.

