#### Data analysis

3.2.8

Data will be analysed using the Statistical Package for Social Sciences (SPSS). An intention‐to‐treat analysis (ITT) will be adopted to manage missing data. Descriptive statistics were conducted to describe the sociodemographic and clinical characteristics of primiparous women by means and standard deviations (SDs); frequencies and proportions. The chi‐square (χ2) and the independent sample *t* test will be used to detect any significant difference between the study and control groups on the baseline variables. Adjusted for possible confounding factors of sociodemographic variables, the repeated measures triply MANCOVA will be conducted to determine whether the intervention of ISP is effective in enhancing *MSE* and social support and for reducing PPD across the three time points of data collection (baseline, post‐test 1, and post‐test 2). The independent *t* test will be used to compare how satisfied the intervention group and the control group are with the health care that they received after childbirth on the two time points of immediately after the intervention and 12 weeks after intervention.

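### Women come from two hospitals, but no stated analysis uses hospital; adding it to the satisfaction comparison and the MANCOVA is a nearly free, small improvement

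*Protocol article*

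**What the plan says.** Section 3.2.2 places the trial in two university-affiliated "tertiary public hospitals in China, where the live births in each study hospital are over 2,000 babies per year". It sets the size: "A minimum of 258 women (129 in each group) are required". How the women will divide between the hospitals is not given.

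Section 3.2.4 gives the tool and the ratio ("The Research Randomizer will be used to randomly assign participants into the experimental group and the control group with a distribution ratio of 1:1") and the concealment ("The allocation sequence will be put into the opaque and sealed envelopes"). It neither mentions nor excludes hospital strata, blocks, or a separate list per hospital.

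Section 3.2.5 makes hospital staff part of the comparator: "Routine care consists of supports from the obstetricians and obstetric nurses during the" inpatient stay. Home visits by community doctors follow.

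Section 3.2.6 lists the social-demographic and clinical data to be collected, and hospital is not in that list. By section 3.2.7, satisfaction is collected only at the two post-tests, so it has no baseline value.

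Section 3.2.8 states two effectiveness analyses. The repeated measures MANCOVA for self-efficacy, social support and depression is adjusted for sociodemographic variables. An independent t test, with no covariate named, is used to "compare how satisfied the intervention group and the control group are with the health care" at each of the two post-test times.

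**The concern.** Women at the two hospitals meet different obstetric staff and may differ in background, so outcomes may differ by hospital. Satisfaction with care is a plausible case. If they do differ, an analysis that omits hospital has one of two weaknesses, depending on how the list was made:

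- **List not stratified by hospital.** The hospital mix of the arms varies by chance, and an unadjusted comparison carries that imbalance into the estimate. Hospital variance also stays in the error term.
- **List stratified by hospital.** The mix is balanced, but a t test that ignores the strata overstates its standard error, so the precision gained by stratifying is not used.

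The point therefore does not depend on what section 3.2.4 leaves unsaid. It matters most for satisfaction, which has neither a covariate nor a baseline value. In the MANCOVA a hospital gap that stays constant over time largely cancels from the arm-by-time comparison, because baseline is one of the three occasions, so the gain there is probably smaller.

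**Working it through.** **Inputs.** From the article: two hospitals, 129 women per arm randomised, 90 per arm before the 30% attrition allowance, alpha 0.05 (taken as two-sided). Assumed, not in the documents: a hospital gap h of 0.3, 0.5 or 0.8 within-hospital SD, and equal hospital shares (80/20 as a variant).

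**1. The plan's own numbers.** 90 / (1 − 0.30) = 128.6, rounded up to 129; 2 × 129 = 258. This step reproduces. Whether 90 follows from the stated effect size is a separate question and is not used here.

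**2. Hospital variance left in the error term.** With hospital share p, the variance ratio without and with hospital in the model is 1 + p(1 − p)h².
- Equal shares: 1 + h²/4 = 1.02, 1.06, 1.16 for h = 0.3, 0.5, 0.8.
- 80/20 shares: 1 + 0.16h² = 1.01, 1.04, 1.10.

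**3. Chance imbalance if the list is unstratified.** SD of the between-arm difference in hospital share = √(2 × 0.25 / 129) = 0.0623.
- P(difference above 10 points) = 2 × P(Z > 0.10/0.0623) = 2 × P(Z > 1.61) = 11%. An exact count for one fixed 129:129 list shared by two equal hospitals gives about 13%.
- At 80/20: √(2 × 0.16 / 129) = 0.0498, giving 4.5%.
- A 10-point imbalance shifts the unadjusted difference by 0.10h = 0.03, 0.05, 0.08 SD.

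**4. False-positive rate if the list is unstratified.** Averaged over randomisations, simulation (10,000 trials per setting, h = 0, 0.5, 0.8) gave 4.9%, 5.1%, 4.8% for simple allocation and 5.0%, 5.1%, 5.1% for a fixed-size list. The test keeps its level.

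Conditional on a 10-point imbalance at 90 per arm, the true standard error is √(2/90) = 0.1491, because the hospital mix is then fixed. The t test uses 0.1491 × √(1 + h²/4) and rejects beyond c = 1.96 times that value. The error is P(Z > (c − 0.10h)/0.1491) + P(Z > (c + 0.10h)/0.1491).

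| h | c | error by formula | error by simulation |
|---|---|---|---|
| 0.3 | 0.295 | 5.2% | 5.1–5.2% |
| 0.5 | 0.301 | 5.5% | 5.4–5.5% |
| 0.8 | 0.315 | 6.2% | 6.2% |

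**5. False-positive rate if the list is stratified but the t test ignores it.** The error is 2 × P(Z > 1.96 × √(1 + h²/4)).
- h = 0.3: 2 × P(Z > 1.98) = 4.7%
- h = 0.5: 2 × P(Z > 2.02) = 4.3%
- h = 0.8: 2 × P(Z > 2.11) = 3.5%

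A simulation of 10,000 trials gave about 4.1% at both 0.5 and 0.8 SD. One of 200,000 gave 4.4% and 3.5%, in line with the formula, so the formula values are used here. Either way the test is conservative.

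**The case against.** The best case against the point has four parts.

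- **List structure and model terms are often left to a full protocol or analysis plan.** This stands for the randomisation. It does not fully answer the analysis point, because section 3.2.8 positively names the satisfaction test and the type of covariate in the MANCOVA.
- **A randomised comparison needs no hospital adjustment to be valid.** This stands. Chance imbalance is already covered by the test's standard error, and the conditional excess is at most about 1.2 points in the range examined.
- **Nothing documents a hospital gap.** This stands, so the size is a range under assumption.
- **Satisfaction may not be strongly tied to the hospital.** It is a secondary outcome, rated about 3 and 6 months after a stay of 3–5 days and after community home visits, and two of the three questionnaire items quoted are open text. This weakens the case for a large gap but not the case for a nearly free covariate.

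Some stronger readings are tempting. A reader might infer that randomisation is plain, with neither strata nor blocks; section 3.2.4 is silent and does not say so. A reader might infer that arm sizes are left to chance, with a 95% range of 113 to 145. That holds only for independent coin flips, whereas a pre-made sequence and a planned 129 per group fit a fixed list. Even under coin flips, power would fall only from 80.3% to 79.7%. A reader might also compute a 7.9% false-positive rate for a 10-point imbalance at 0.8 SD. That figure keeps hospital variance in the true standard error although the mix is held fixed; the correct value is 6.2%.

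**Conclusion.** The point holds as a small, nearly free improvement and not as an error that threatens the trial. As stated, neither effectiveness analysis in section 3.2.8 uses hospital, although the trial has two. This is a loss whether or not the list is stratified.

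For satisfaction, with equal hospital shares and an assumed gap of 0.3 to 0.8 SD, the loss is about 2 to 16% in error variance. If the list is unstratified, there is also about an 11% chance of an imbalance above 10 points; at 10 points the shift is 0.03 to 0.08 SD and the conditional error 5.2 to 6.2%. If the list is stratified, the error falls to between 4.7% and 3.5% over the same gaps. With a smaller gap or unequal hospital shares, the loss is smaller.

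The documents do not support calling the t test invalid, criticising the arm sizes, or changing the allocation procedure during enrolment.

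**What to change.** In section 3.2.8, replace the satisfaction t test with a linear model containing arm and hospital, fitted at each of the two post-tests. Add hospital as a between-subject factor in the MANCOVA alongside the sociodemographic covariates. State both before the data are analysed.

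Hospital is known from recruitment on the wards, so no new data are needed. The cost is one degree of freedom for hospital and a sentence of text.

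In section 3.2.4, as a matter of reporting only, say whether the sequence was separate for each hospital and whether it was blocked. The allocation itself should stay as it is: recruitment began in May 2020, and an effect of this size does not justify a change during enrolment.
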